### Bias & effect modification

The case–control design is potentially prone to a number of biases [28], in particular some that could confer a bias *in favour* of screening, and which are addressed either at the design stage by choosing appropriate selection criteria, or at the analysis stage by using suitable statistical methods. The selection of participants and choice of analytic measures of exposure (see Participants: selection of cases & controls and Statistical Methods sections, respectively) are crucial to ensure accuracy.

#### Exposure opportunity (frequency) bias

Once diagnosed with cancer, the cases come under clinical management and do not continue with routine screening as before. The controls, however, will continue to attend screening. To avoid a potential bias *in favour* of screening, controls are given a pseudo-diagnosis date that is the same as that of their matched case and screening history is only considered up to that date [29].

In contrast, the fact of the case having necessarily a diagnosis of cancer and a control usually not having such a diagnosis, induces an artificially higher retrospective probability of screening exposure in the cases, a bias *against screening* (i.e. the screen-detected cases will always have this screen recorded at diagnosis, whereas the large majority of controls will not at pseudo-diagnosis date). Simply excluding the detection screens of the cases from the histories would bias the results *in favour* of screening. A driver of this bias is prevalence screening and, as the NHS BCSP is a relatively young programme with at most 3 rounds at the planned start of the pilot phase (January 2012), this bias may initially be present although it is likely to decrease for subsequent evaluations.

The extent of screening opportunity bias will be investigated first, by applying an analytical correction to the odds ratio using the method developed by Duffy and collaborators [30], and second, by performing sensitivity analyses in which the date of pseudo-diagnosis for controls whose matched cases have had a screen-detected *index diagnosis* will be extended by up to 3 years, the estimated average sojourn time for each screen-detected case, to counteract the artificially higher retrospective probability of screening exposure in cases [29]. A shorter sojourn time may however be more appropriate for screen-detected tumours of stage Duke B or worse [31].

In addition, we will perform a sensitivity analysis using screen-detected cases only. We will aim to establish whether such cases were screened less often in the past than matched controls who were screened at the time of detection screen of the case [32, 33]. In this analysis, controls that have had a screen in the same year as the *index screen* (detection screen) of their matched case will be included. The *index screen* will be excluded and the effect of prior attendance at screening on incidence of advanced stage primary CRC will be investigated. The impact of being invited to bowel cancer screening prior to *index screen* on CRC incidence may also be investigated.

But the major source of bias in case–control studies where controls are selected from the general population is potential self-selection bias [34].

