**Design 5**			
	Previous diagnosis	None	None
		CRA	CRA
	Index diagnosis	Any CRC (Duke A-D)	_
		Screen-detected	Last screened in same year as case index screen
	Analysis	Exposure to screening prior to *index diagnosis* of case	
		Controlling for previous history of CRA	

CRA: Colorectal Adenoma; CRC: Colorectal Cancer.

Duke A CRC: CRC diagnosed at stage Duke A; Duke B+ CRC: CRC diagnosed at stage Duke B, C or D.

Matched general population controls will be restricted to those individuals who have never had stage B or worse primary CRC, but may have had early stage primary CRC (Duke’s stage A) or CRA prior to and including the case's date of *index diagnosis*. The majority of controls, will, however, never have had CRC (or CRA). In later stages of the evaluation, all incident cases will be considered (Design 4).

All cases and controls will appear on the HSCIC database at Exeter and will have available data on bowel, cervical (for women aged 60–64) and breast (for women aged 60–74) screening strictly prior to the date of *index/first diagnosis* of the case, depending on the analysis (that is, they have been invited to screening at least once prior, see Table 1 for details). Bowel, cervical and breast screening history as well as primary CRC pathology variables will be retrieved for all cases and controls. In addition, history of previous CRA and corresponding tumour pathology variables will be obtained.

A detailed description of the subject selection criteria and matching algorithm will be created in collaboration with our NHS partners.

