Secondary analyses will consider time since last screen stratified by age at diagnosis/pseudo-diagnosis, by *index/first tumour* detection mode, and by region (Main phase only). Analysis may be adjusted for stage at diagnosis. The effect of attending a screen in a particular 5-year age band (e.g. 60–64), in the pilot phase, or 2-year age band (e.g. 60–61), in the main phase, on incidence from advanced stage primary CRC in the subsequent 5-year age band (i.e. 62–66 or 65–69, respectively) will also be investigated, as performed for the cervical screening audit [17]. The results of this analysis should be very similar to those obtained from the analysis of ‘time since last screen’ after stratifying the analysis by age at diagnosis/pseudo-diagnosis.

In the main phase of the study, the effect of invitation to bowel screening and attendance at screening prior to the *index screen* of the case will also be assessed among screen-detected cases matched to controls screened within the same screening interval (Table 1 Design 5).

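### The screen-detected-only analysis compares detection at repeat and first screens, so its any-CRC odds ratio is expected below 1 even if screening prevents no cancer

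*Protocol article*

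**What the plan says.** In the section on exposure opportunity (frequency) bias, the Protocol article states that "we will perform a sensitivity analysis using screen-detected cases only". The aim is put as follows: "We will aim to establish whether such cases were screened less often in the past than matched controls". Controls must have had a screen in the year of the case's detection screen. That index screen is left out, and then "the effect of prior attendance at screening on incidence of advanced stage primary CRC will be investigated". The section adds that the impact of earlier invitation on CRC incidence may also be examined.

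Table 1, Design 5 sets out this comparison with a different case definition: any CRC, Duke A to D. Controls are "Last screened in same year as case index screen", and the only previous diagnoses allowed are none or adenoma (CRA). The Statistical methods section places Design 5 in the main phase, where the effect of earlier invitation and attendance "will also be assessed among screen-detected cases matched to controls screened within the same screening interval".

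The same bias section says of exposure opportunity bias in the main comparison, which it describes as a bias against screening: "A driver of this bias is prevalence screening". It also warns that simply excluding the cases' detection screens would bias in favour of screening. It does not discuss what earlier screens do to the pool of cancers available for detection at the index screen.

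**The concern.** Everyone in this analysis is screened at the index round. The odds ratio for earlier attendance therefore compares the chance of a cancer being found at a repeat screen with the chance at a first screen. A cancer found at an earlier screen cannot become an index-screen case later, because Design 5 excludes previous CRC. It is still an incident cancer, only counted earlier. Repeat attenders reach the index screen with a depleted pool and first attenders with a full one.

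The odds ratio would then fall below 1 in a programme that only brings diagnosis forward. For any CRC this is a realistic case: the Background section reports that the randomised trials generally found no significant effect on incidence after 14 to 20 years. The analysis is offered as a check on bias and largely avoids the attender versus non-attender contrast, so readers are likely to give it weight. Described as an effect on incidence, a low odds ratio could be taken as support for the primary result when it shows only earlier detection.

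**Working it through.** The document gives no expected odds ratio or sample size for this analysis, so there is no figure of its own to reproduce.

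**Inputs**
- Screening interval t = 2 years (Statistical methods).
- Mean preclinical sojourn m = 3 years (exposure opportunity section), or 2 years, which Statistical methods gives as approximating the preclinical screen-detectable period.
- Duke B+ sojourn: the exposure opportunity section says a shorter value may be appropriate but gives none. Assumed 1 to 2 years.
- Test sensitivity S: not in the document. Assumed 0.5, range 0.3 to 0.7.
- Number of prior screens: one in the base case. The programme had at most three rounds by January 2012.

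**No-effect model.** Constant onset rate, exponential sojourn, independent test results at successive screens, and no cancer prevented. Of the preclinical cancers present just before the index screen, a fraction exp(-t/m) was already present t years earlier. A share S of that fraction was found and removed. Sensitivity at the index screen cancels, so the detection-rate ratio, repeat versus first, is

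OR0 = 1 - S × exp(-t/m).

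**Any CRC, one prior screen two years earlier**

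| m (years) | exp(-2/m) | S = 0.3 | S = 0.5 | S = 0.7 |
|---|---|---|---|---|
| 3 | 0.513 | 0.85 | 0.74 | 0.64 |
| 2 | 0.368 | 0.89 | 0.82 | 0.74 |

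For example, 1 - 0.5 × 0.513 = 0.743. A simulation of the same model gave 0.744.

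**Number and timing of prior screens.** With e = exp(-t/m) and r(0) = 1, the recursion is r(k+1) = (1 - e) + e × (1 - S) × r(k). At S = 0.5 and m = 3 this gives 0.74, 0.68 and 0.66 for one, two and three prior screens. One prior screen four years earlier gives 1 - 0.5 × exp(-4/3) = 0.87.

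**Shape of the sojourn.** A two-stage simulation (Duke A then B+, total mean 3 years, S = 0.5 at both stages) gave 0.78 for any CRC, against 0.74 under a single exponential.

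**Advanced stage.** Here only cancers already Duke B+ at the earlier screen are removed artefactually. Cancers caught at Duke A before progressing are the benefit under study. In the two-stage simulation at S = 0.5:

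| Mean Duke A / B+ sojourn (years) | Total advanced-stage OR | OR from removing already-B+ cancers only |
|---|---|---|
| 2 / 1 | 0.70 | 0.93 |
| 1.5 / 1.5 | 0.69 | 0.87 |
| 1 / 2 | 0.70 | 0.82 |

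The last column agrees with the closed form using the B+ sojourn alone: 1 - 0.5 × exp(-2/1) = 0.93, 1 - 0.5 × exp(-2/1.5) = 0.87 and 1 - 0.5 × exp(-2/2) = 0.82. Over S = 0.3 to 0.7 and a B+ sojourn of 1 to 2 years, the artefact alone runs from 0.96 to 0.74.

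**The case against.** The strongest reply has four parts.

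- **It is a supporting analysis.** It is called a sensitivity analysis in the bias section and appears with the secondary analyses in Statistical methods. The document states no test against 1 and no decision rule. This stands. A reader might infer that the plan commits to claiming prevention from any value below 1, but it does not say so. What remains is that it calls the comparison an effect on incidence and sets no limit on how it may be read.
- **The authors already deal with bias from dropping detection screens.** Requiring controls to be screened in the same year does answer that warning. It does not answer depletion, which arises because both groups are screened at the index round. The method is cited to earlier literature and the SAP is not shown, so interpretive limits may exist elsewhere. None appears in the article.
- **The attendance analysis in the bias section names advanced-stage CRC.** This stands and narrows the point. A reader might carry 0.74 over to that outcome, but that would count interception at Duke A as artefact.
- **Matching on year of first invitation makes many sets uninformative.** Where neither the case nor the controls could have had a prior screen, the set adds nothing to a conditional analysis. This affects precision more than the expected odds ratio. It is one reason to quote no false-positive rate here: the document gives neither the number of screen-detected cases nor prior attendance among same-year attenders.

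**Conclusion.** The concern holds in a limited form. For the any-CRC outcome of Design 5, an odds ratio below 1 is expected if screening prevents nothing. The direction needs only that an earlier screen detects some cancers that would still be preclinical at the index screen. The size depends on assumptions: 0.64 to 0.89 for sensitivity 0.3 to 0.7, a sojourn of 2 to 3 years and one prior screen two years earlier. The value 0.74 is one point in that range (S = 0.5, m = 3) and is not a figure from the document; the two-year preclinical period gives 0.82 at the same sensitivity.

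For advanced-stage CRC the artefact is about 0.82 to 0.93 at S = 0.5 and a B+ sojourn of 1 to 2 years. Any further reduction through interception at Duke A is genuine.

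A reader might infer that the primary odds ratio is compromised. It is not: it comes from a different comparison that keeps the detection screens. What is at risk is the interpretation of a secondary analysis, which should be corrected before results are seen.

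**What to change.** In the exposure opportunity section, in Statistical methods and in Table 1, Design 5:

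1. State that the odds ratio is the relative detection rate at repeat versus first screens. Do not interpret an any-CRC value below 1 as a reduction in incidence, or as corroboration of the primary result.
2. Report beside it the no-effect value 1 - S × exp(-t/m), adapted to the number and timing of prior screens, over a stated range of S. Use the overall sojourn (2 to 3 years) for any CRC and only the shorter Duke B+ sojourn for advanced stage. Present this as a sensitivity range and not as a pass/fail rule: a threshold built on the 3-year sojourn would count real stage-shift benefit as artefact.
3. Reconcile the outcome, which is advanced-stage CRC for attendance in the bias section and Duke A to D in Design 5. If both are intended, say so and report them separately.

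The cost is wording and a few lines of code, with no new data. The drawback is that the benchmark depends on assumed sensitivity and sojourn time, and the result will look less favourable.

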#### Self-selection (volunteer) bias

Individuals who accept the invitation to screening (attenders) may have an a priori better health status compared with individuals who do not (non-attenders). In the case of bowel screening, gFOBt kit return has been shown to be significantly lower for postcode sectors with poor health [35]. Therefore attenders at screening may be less likely to acquire and potentially die from colorectal cancer. We would anticipate that this will confer a bias *in favour* of screening. Although this bias *in favour* of screening is unavoidable at the design stage, it can be approximately corrected for in the statistical analysis.The regression analyses will be with adjusted for the Index of Multiple Deprivation (IMD), an area-based measure of relative deprivation, derived from residents’ postcodes based on census statistics for overcrowded housing and other factors, and believed to be the main confounding factor relating to both the exposure (i.e. the decision to attend screening), and the outcome.The method developed by Duffy and collaborators [36] will be used *for all patients* to correct the estimated odds ratio using data on participation from the RCTs of CRC screening, in particular data from the Nottingham trial (Individual data obtained for the Nottingham trial from the authors [name] & [name]). In addition, data from regions with population characteristics (total population of screening age 60–69, deprivation, ethnicity, urbanisation status) comparable to areas offered gFOBt screening may be collected from the early stages of the NHS BCSP implementation (e.g. 2006–2007) when the programme had not been fully rolled out [9]. The following estimates may then be derived to potentially help adjust for self-selection bias: (i) CRC incidence among invited (region 1) screened individuals (i.e. risk among attenders), (ii) CRC incidence among invited (region 1) individuals who were not screened (i.e. risk in non-attenders), and (iii) CRC incidence among individuals who were not invited (and not screened, region 2).The method developed by Duffy and collaborators [36] will also be used *for women only* to correct the estimated odds ratio using data on participation in the NHS CSP (cervical) and/or NHS BSP (breast) screening programmes, rather than data on participation from the RCTs of mammographic screening. In the absence of self-selection, the relative risk of primary CRC (death/incidence) associated with bowel cancer screening for non-attenders at cervical or breast screening would be expected to be equal to the relative risk in cervical or breast screening attenders (after adjusting for bowel cancer screening). In the Nottingham RCT, the incidence of primary CRC (all stage) was about 13% higher in non-attenders to bowel cancer screening compared to attenders (Individual data obtained for the Nottingham trial from the authors [name] & [name]). The crucial element in correcting for self-selection bias is the risk ratio for non-attenders versus attenders to breast/cervical screening. Thus the correction is estimated only from data on women as both other screening programmes apply to women only. This will be calculated for women who attended bowel screening at least once and for women who did not attend a single screen, to control for attendance at bowel cancer screening. A range of denominator values for the risk ratio will be assessed for sensitivity. One could compare primary CRC rates (i) in women who have had breast/cervical screening - but not bowel screening -with women who have had neither breast/cervical nor bowel screening; and (ii) in women who have had *both* breast/cervical and bowel screening with women who have only had bowel screening.

Data for women with age at diagnosis/pseudo-diagnosis between 60 and 69 year-old who would have been invited to both the bowel and breast screening programmes will be used. Alternatively, data for women with age at diagnosis/pseudo-diagnosis between 60 and 64 year-old who would have been invited to both the bowel and cervical screening programmes will be used. Also, in women under age 60, one could compare primary CRC rates in women who have, or have not had, breast/cervical screening, hence by-passing the positive confounding between uptake of the various screening programmes.

The national average participation rate at bowel cancer screening will be obtained for men and women from the NHS Annual Report on Bowel Cancer Screening [37, 12]. For the pilot phase, a single self-selection factor will be estimated as the data will cover one region only; for the national phase, regional factors may be estimated to assess variation in self-selection between regions.

Self-selection will be also addressed at an individual woman level by adjusting the regression model for participation in the other screening programmes, with careful adjustment for the confounding between attendances in different programmes.

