**Methods/Design:**

All incident cases of primary colorectal cancer in England will be included. Cases will be matched to controls with respect to sex, age, area of registration and year of first invitation to screening. Each evaluation round will cover a 2-year period, starting from January 2012, and ongoing thereafter. In the first instance, a pilot will be carried out in a single region. Variables related to colorectal tumour pathology will be obtained to enable selection and matching of cases and controls, and to allow analyses stratification by anatomical subsite within the bowel. Cases at Duke’s stage B or worse will be considered as "advanced stage". The influence of sex will also be investigated. The incidence ratio observed in randomised controlled trials between controls (not invited) and non-attender invitees will be used to correct for self-selection bias overall. Screening participation at other national screening programmes (cervical, breast) will also be collected to derive a more contemporaneous adjustment factor for self-selection bias and assess consistency in self-selection correction in female patients.

Full ethical approval was obtained from the Health Research Authority.

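### If the trial-based self-selection factor is applied to an IMD-adjusted odds ratio, as the text plainly reads, the deprivation part of self-selection is removed twice and the benefit of screening is understated

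*Protocol article*

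**What the plan says.** The section Self-selection (volunteer) bias sets out several remedies for the same bias.

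- **Regression adjustment.** "The regression analyses will be with adjusted for the Index of Multiple Deprivation (IMD), an area-based measure of relative deprivation". No analysis is exempted. IMD is "believed to be the main confounding factor relating to both the exposure (i.e. the decision to attend screening), and the outcome".
- **External correction.** A published correction method is planned for the whole study population, men and women alike. Its purpose is stated as "to correct the estimated odds ratio using data on participation from the RCTs of CRC screening, in particular data from the Nottingham trial". The Abstract (Methods/Design) defines the quantity: "The incidence ratio observed in randomised controlled trials between controls (not invited) and non-attender invitees will be used to correct for self-selection bias overall". The size given is that "the incidence of primary CRC (all stage) was about 13% higher in non-attenders to bowel cancer screening compared to attenders".
- **Women only.** A second version of the correction takes its ratio from breast and cervical screening attendance. Separately, "Self-selection will be also addressed at an individual woman level by adjusting the regression model for participation in the other screening programmes".

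Statistical methods names conditional logistic regression as the analysis and describes no other source of an odds ratio. The protocol does not say whether the odds ratio to be corrected is the one with or without IMD, whether the trial ratio is adjusted or standardised for deprivation, or whether the factor is meant to cover only the self-selection left after IMD adjustment.

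**The concern.** The external factor measures how far non-attenders differ in risk from the whole uninvited population. Unless it is adjusted, it contains every reason for that difference, including deprivation. An odds ratio from a regression with IMD in it has already lost the deprivation part. Multiplying that odds ratio by the full factor removes the deprivation part a second time.

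The protocol's own view of IMD as the main confounder suggests that the overlap need not be small. Both steps move the odds ratio towards 1, so the error runs against the programme being evaluated. The main phase expects considerable precision (Power calculation). A systematic shift of this kind would not be covered by the confidence interval, and a narrow interval could sit around a biased value.

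**Working it through.** **Inputs from the protocol**
- Planning odds ratio 0.8. It reproduces from the discordant cells of Table 3: 16/20 = 0.80. It is used here as an illustrative crude odds ratio.
- Control exposure 59% (Table 3), taken as attendance a = 0.59.
- Incidence ratio of non-attenders to attenders, 1.13, all stages (Self-selection section).

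The protocol gives no corrected odds ratio, so there is no further figure of its own to reproduce.

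**Assumptions not in the documents**
- s, the share of log(1.13) carried by IMD: range 0 to 1.
- Screening leaves overall incidence unchanged, so that 1.13 reflects self-selection only.
- The all-stage ratio also applies to Dukes B or worse.

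**Step 1: turn 1.13 into the ratio defined in the Abstract.** Set the uninvited risk to 1. The risk in non-attenders relative to the uninvited is

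D = 1.13 / (a + (1 − a) × 1.13) = 1.13 / (0.59 + 0.41 × 1.13) = 1.13 / 1.0533 = 1.0728.

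**Step 2: the correction factor.** Under self-selection alone, attenders have risk (1 − (1 − a)D)/a. The corrected odds ratio is therefore

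OR × D × a / (1 − (1 − a)D) = OR × (1.0728 × 0.59) / (1 − 0.41 × 1.0728) = OR × 1.13.

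The factor stays at 1.13 for attendance of 50% to 60% (D from 1.061 to 1.074).

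**Step 3: one consistent correction.** 0.80 × 1.13 = 0.904. The same value follows from an IMD-adjusted odds ratio, 0.80 × 1.13^s, with the matching residual factor 1.13^(1−s).

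**Step 4: IMD adjustment followed by the full factor.** The result is 0.80 × 1.13^s × 1.13, an overshoot of 1.13^s.

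| s | IMD-adjusted OR | After full factor | Log benefit lost relative to 0.904 |
|---|---|---|---|
| 0 | 0.800 | 0.904 | 0% |
| 0.25 | 0.825 | 0.932 | 30% |
| 0.5 | 0.850 | 0.961 | 61% |
| 0.75 | 0.877 | 0.991 | 91% |
| 1 | 0.904 | 1.022 | all, and past 1 |

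**Step 5: the same error when the true odds ratio is 0.80.** The doubly corrected value is 0.80 × 1.13^s: 0.825, 0.850, 0.877 and 0.904 at s = 0.25, 0.5, 0.75 and 1. The log benefit lost is 14%, 27%, 41% and 55%.

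**Step 6: when the benefit would vanish.** This needs a true odds ratio of at least 1.13^(−s): 0.885 at s = 1, 0.941 at s = 0.5. Starting from a crude 0.80, it needs s of at least log(1/0.904)/log(1.13) = 0.83.

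**The case against.** The strongest reply is that the article leaves a detail open and does not fix an error. It never calls the trial ratio crude. It does not say that the odds ratio being corrected is the IMD-adjusted one, and it fixes no order for the steps. Individual data from the Nottingham trial were obtained, so an adjusted factor may be possible. The correction is described as approximate and several routes are planned. All of this is true, and it makes the finding conditional on the plain reading. It does not remove it: the regressions are adjusted for IMD without exception, they are the only described source of an odds ratio, and nothing restricts the factor to residual self-selection. The planned sensitivity range belongs to the women-only risk ratio and does not address the overlap.

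Four further points stand.

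- **s is unknown.** Calling IMD the main confounder gives no share. The protocol gives no figure for IMD and CRC incidence, so s could be near 0.
- **The 13% is an imperfect input.** It covers all stages and compares non-attenders with attenders, whereas the Abstract's ratio is against uninvited controls. Step 1 needs the stated assumption to connect them.
- **Matching matters too.** Controls come from the same NHAIS area, so the matched odds ratio without IMD may already have lost some of the deprivation effect. The value 0.904 is itself approximate.
- **Women.** A reader might infer that a full factor is also applied to an odds ratio already adjusted for breast or cervical attendance. The text does not say so; the individual-level adjustment may be a separate analysis.

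A reader might also infer that the plan erases a real benefit. The documents do not support that as a general statement: it requires a high s together with a weak true effect (Step 6).

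**Conclusion.** The point holds as a conditional one. Followed as plainly written, the plan corrects for the deprivation part of self-selection twice and understates the benefit of screening. The overshoot is 1.13^s, at most 1.13, given the all-stage 13% excess, no effect of screening on overall incidence, and s between 0 and 1. That is large enough to matter next to a planning odds ratio of 0.8, but at a true odds ratio of 0.80 the benefit remains visible. The need for matching adjustment follows from the algebra above and does not rest on any reading of the cited method. Because the article fixes both components for all patients, this is more than a detail left to a fuller document.

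**What to change.** State that the odds ratio and the self-selection factor must carry the same adjustment for deprivation, and use one of two pairs:

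1. The unadjusted trial factor with the matched odds ratio from a model without IMD. This is approximate, because area matching may already remove some deprivation.
2. An IMD-adjusted factor with the IMD-adjusted odds ratio. The factor could come from the individual trial data, if they hold deprivation, or from the in-study breast/cervical comparison with IMD in the model. The latter is estimated in women only, so using it for men would be a further assumption.

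Name which pair is primary. Report the IMD-adjusted odds ratio without any factor as a separate result. State that no full factor is applied to an odds ratio already adjusted for breast or cervical screening participation.

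The cost is wording and one extra model fit. If the first pair is primary, the headline odds ratio no longer carries IMD adjustment in the regression. The second pair depends on data whose content the protocol does not describe.
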